**Figure 1 F1:**
[figure not shown]
Recruitment and flow within Cohort 1 within the YORKSURe study: male and female participants will be solely recruited from the YLST. USS, ultrasound scan; YLST, Yorkshire Lung Screening Trial.

Eligibility for Cohort 2: Men aged 65–79 identified through a database search at 8–10 selected GP practices considered to be in high-risk BCa mortality areas in South Yorkshire (figure 2).

**Figure 2 F2:**
[figure not shown]
Recruitment and flow within Cohort 2 of the YORKSURe study: male participants will be invited from populations at risk of high-mortality from bladder cancer. USS, ultrasound scan.

Eligibility for Cohort 3: men and woman will be identified via local urology departments when a referral is made for a 2ww urology appointment for investigation of haematuria (figure 3).

**Figure 3 F3:**
[figure not shown]
Participant flow within Cohort 3 of the YORKSURe study: male and female patients undergoing investigation within the NHS for haematuria (according to the 2 week-wait criteria within the National Institute of Care Excellence guidelines) will be invited to participate.

### Exclusion criteria

#### Cohort 1

Unable to or did not consent to contact from other research teams.Insufficient capacity to give consent to take part in the research as determined by the investigator taking consent.

#### Cohort 2

Participant has opted out of their NHS data being used for research via the National Data Opt-Out.Prior diagnosis of bladder or kidney cancer.Diagnosis with any other cancer within the past 5 years (except non-melanoma skin cancer).Insufficient capacity to give consent to take part in the research, defined as the presence of the following conditions coded in the GP records: dementia, Alzheimer’s disease or Parkinson’s disease; or as determined by the investigator taking consent.

#### Cohort 3

Unable to provide written informed consent.Insufficient capacity to give consent to take part in the research, defined as the presence of the following conditions coded in the GP records: dementia, Alzheimer’s disease, or Parkinson’s disease; or as determined by the investigator taking consent.Evidence in patient medical record of historic dissent to use of data in research or participant has opted out of data use via the National Data Opt-Out.

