### Research need

YORKSURe is a feasibility trial aimed at the early diagnosis of BCa through the detection of haematuria in asymptomatic individuals at high risk of mortality from the cancer. Following results of the feasibility trial, the aim is to conduct a large-scale trial, with sufficient power to test any differences in BCa mortality. However, to undertake this successfully, we need to understand if our proposed approach is robust, appropriate, necessary and acceptable to participants. Here we detail the trail using Protocol V.5.0 date 16 January 2023.

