#### Study aims and objectives

Three cohorts will be studied in this feasibility study. Each will address a separate aim, all of which are needed to develop a phase III prospective trial:

Aim 1: Cohort 1 will test compliance, prevalence of haematuria and BCa and the economics of the trial within a screening-engaged population. It might suggest that BCa screening works best when embedded within lung screening services. It will also test women and populations younger than typical for the highest risk BCa age group.Aim 2: Cohort 2 will test compliance, prevalence of haematuria and BCa, prevalence of glycosuria and undiagnosed diabetes within a high-risk community-based population.Aim 3: Cohort 3 will provide a positive predictive value (PPV) of the study tests (urine self-testing, urine cytology and ultrasound) as assessed in a population already referred in the NHS 2ww haematuria pathway.

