## Methods and analysis

### Study design and setting

Eligibility for Cohort 1: men and women aged 55–80 years who are registered with a GP within the Leeds Clinical Commissioning Group area, who are part of the Yorkshire Lung Screening Trial^24^ and have given consent to be contacted by other research teams (figure 1).

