### Primary outcomes

This is a feasibility study and so there are multiple primary outcomes reflecting each stage of the study and what we need to understand for a larger phase III randomised controlled trial:

1. Acceptability of urine self-testing and the Early Detection Clinics will be measured by:

1.1. Proportion of invitees who report results for at least one test strip.

1.2. Proportion of participants who attend and consent for cytology and urinary tract ultrasound following detection of haematuria on self-testing.

1.3. Proportion of participants who attend and consent for HbA1c blood testing following the detection of glycosuria on self-testing.

2. Compliance with urine self-testing will be measured by;

2.1. The proportion of participants who report results for (i) all six test strips and (ii) three or more test strips.

2.2. The number of test strips returned on average in those who return at least one test strip.

3. Prevalence of haematuria will be measured from the proportions of participants with ≥1 test strip positive for haematuria.

4. Prevalence of glycosuria will be measured from the proportions of participants with ≥1 test strip positive for glycosuria.

5. Haematuria clinic outcomes will be measured via:

5.1. The proportion of participants with a positive or abnormal cytology in those where a urine sample is collected.

5.2. The proportion of participants who have an abnormal USS, who underwent scanning.

6. Glycosuria clinic outcomes will be measured via the proportions of those with an elevated HbA1c following collection of a blood sample.

7. Urinary symptoms will be measured via symptom scores from the urine symptoms questionnaire (as completed prior to self-testing).

8. BCa in the tested population will be measured via the proportions of BCa cases and corresponding stage in identified participants (excluding non-responders and withdrawals).

9. The accuracy of self-testing, cytology and USS will be measured via:

9.1. The sensitivity, specificity, PPV and negative predictive value (NPV) of the following in men and women with cancer as identified by cystoscopy results at the 2ww appointment

9.1.1. Self-testing (App vs freephone).

9.1.2. Cytology and ultrasound (separately and in combination) as a triage test in those with positive haematuria

9.2. The predictive value of symptoms in combination with self-testing:

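### Cohort 1 does not exclude prior bladder or kidney cancer although Cohort 2 does, so known or recurrent cancers can be counted in its bladder cancer yield, stage mix and PPV

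*Protocol article*

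**What the plan says.** Under Study design and setting, Cohort 1 admits "men and women aged 55–80 years who are registered with a GP within the Leeds Clinical Commissioning Group area" who belong to the Yorkshire Lung Screening Trial and agreed to be contacted by other research teams. No condition on cancer history is given. Under Exclusion criteria, Cohort 1 has two entries: "Unable to or did not consent to contact from other research teams" and "Insufficient capacity to give consent to take part in the research as determined by the investigator taking consent".

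The Cohort 2 list in the same section is longer. It contains "Prior diagnosis of bladder or kidney cancer" and also excludes any other cancer diagnosed in the previous five years, non-melanoma skin cancer apart.

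Both cohorts report the same cancer outcome. Aim 1 states that "Cohort 1 will test compliance, prevalence of haematuria and BCa and the economics of the trial within a screening-engaged population", and Aim 2 sets haematuria and bladder cancer prevalence for Cohort 2. Primary outcome 8 reads "BCa in the tested population will be measured via the proportions of BCa cases" with their stage, leaving out non-responders and withdrawals only. The Statistical analysis section adds PPVs and NPVs of the haematuria test for Cohorts 1 and 2.

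**The concern.** The article describes the trial's purpose as "early diagnosis of BCa through the detection of haematuria in asymptomatic individuals at high risk of mortality from the cancer". A cancer that was already diagnosed before the kit arrived, or a recurrence of one, is not an early detection by screening. Someone under follow-up for bladder cancer may also be more likely than others to have a positive strip, abnormal cytology and a bladder cancer entry in urology or registry records.

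If such people enter Cohort 1 and are counted, three results stop meaning what a screening study needs them to mean:

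- **Yield.** It mixes new detections with known disease.
- **Stage mix.** It includes cancers whose stage was not set by screening.
- **PPV.** A positive strip in a person with known cancer is credited to the test.

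These figures go further than the feasibility report. The Economic evaluation section says the model will be parameterised with the feasibility outcome data, so an inflated yield would be carried into it and into the design of the later trial. Few cancers are expected, so one or two known cases change the estimate visibly.

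**Working it through.** **Step 1: is the gap closed elsewhere in the article?**

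| Section | What it could have done | What it does |
|---|---|---|
| Study design and setting | Require no prior urological cancer | Age, GP registration, parent trial membership, consent to contact |
| Exclusion criteria, Cohort 1 | Exclude it | Two entries, neither on cancer history |
| Investigation of haematuria | Separate new from recurrent disease | One bladder cancer diagnosis category |
| Data collection | Record cancer history | Not among the questionnaire or clinic items listed |
| Data collection, registry | Date prior diagnoses | Passive follow-up at 1, 2 and 3 years after trial end; no first-diagnosis rule |
| Primary outcome 8 | Remove known cases | Removes non-responders and withdrawals only |
| Statistical analysis | Restrict yield and PPV to new disease | No such restriction |

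The article does not close the gap.

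**Step 2: how many cases are expected?** The article states no expected yield, so there is no figure of its own to reproduce. The inputs are the Cohort 1 enrolment of 800 out of 2000 invited (Sample size) and the earlier British screening study cited in the Introduction, with 17 cancers in 2356 men.

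- Yield: 17 / 2356 = 0.72%.
- Expected new cases: 800 × 17 / 2356 = 5.77, about 5.8.

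This benchmark comes from men. Cohort 1 includes women and, by Aim 1, people younger than the highest-risk group, so 5.8 may be too high. A lower base would make the percentages below larger.

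**Step 3: what would known cases add?** Two quantities are assumptions, not figures from the article: the share of enrolled participants with prior bladder cancer (0.3% to 1.0%) and the fraction of those who end up counted (25% to 100%).

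Extra cases = 800 × share × fraction. Rise = extra cases / 5.77.

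| Prior share | People | 25% counted | 50% counted | 100% counted |
|---|---|---|---|---|
| 0.3% | 2.4 | 0.6 (+10%) | 1.2 (+21%) | 2.4 (+42%) |
| 1.0% | 8 | 2.0 (+35%) | 4.0 (+69%) | 8.0 (+139%) |

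**Step 4: the same in the planned reporting format.** With 95% Wilson intervals and a base of 6 whole cases in 800:

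- No known cases: 6/800 = 0.75% (0.34% to 1.63%).
- Two known cases counted: 8/800 = 1.00% (0.51% to 1.96%).
- Eight known cases counted: 14/800 = 1.75% (1.05% to 2.92%).

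The intervals overlap, but an interval reflects sampling error only and would not reveal the added cases.

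**Step 5: haematuria prevalence.** The change is share × (haematuria rate with prior cancer − background rate). Assume a background of 10% to 20% and a rate of 30% to 60% with prior cancer.

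- Smallest: 0.003 × (0.30 − 0.20) = 0.03 percentage points.
- Largest: 0.010 × (0.60 − 0.10) = 0.5 percentage points.

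This is small for a prevalence of 10% or more.

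**The case against.** **The parent trial may already filter these people.** Cohort 1 is drawn solely from lung screening trial participants, and that trial's eligibility rules are not shown. This stands as a limit: whether known bladder cancers enter, and how many, cannot be settled here. The article does not say that it relies on such a filter.

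**An article leaves analysis-set rules to the full protocol or SAP.** This is fair for detailed rules on incident cases. The point here is different: the article sets out eligibility cohort by cohort, and the stated criteria differ between two screening cohorts that report the same primary outcome, without a reason.

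**Stronger readings that a reader might infer.** The document does not support these:

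- *Known cases will dominate the yield, with inflation up to 139%.* That figure needs the top of an unsourced range and every prior case counted. To be counted through the clinic, a person must test positive, attend, have an abnormal scan or cytology, be referred, and be given a bladder cancer diagnosis.
- *The registry extract will count lifetime diagnoses.* The linkage is described as passive follow-up. The article does not say that earlier registrations will be included.
- *Haematuria prevalence is seriously distorted.* Step 5 shows a minor effect.
- *A planned Cohort 1 versus Cohort 2 comparison is biased.* Estimates are to be given per cohort and no formal contrast is specified. Aim 1 only raises the possibility that screening works best within lung screening services. The cohorts also differ in sex, age, area and recruitment route, so removing prior cases would not by itself make them comparable.

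**Conclusion.** The point holds in a limited form. On the stated criteria, people with prior bladder or kidney cancer can enter Cohort 1 but not Cohort 2, and outcome 8 as worded does not remove them. Cohort 1's yield, stage mix and PPV can therefore include known or recurrent disease, unless the parent trial's eligibility prevents it.

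The size is uncertain. The working range of roughly 10% to 139% on about 5.8 expected cases rests on the transferred 17/2356 yield, an assumed prior-cancer share and an assumed counted fraction. It shows that a few people could matter; it does not estimate the bias. The defect should be corrected because it touches a primary outcome in a study meant to inform a screening trial, and because it can be handled at analysis.

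**What to change.** 1. For the Cohort 1 analysis of outcome 8 and of PPV/NPV, apply the prior bladder or kidney cancer exclusion already written for Cohort 2.
2. In that analysis, count only first bladder cancers diagnosed on or after the self-test date.
3. Take diagnosis dates from urology records and from the registry request. The linkage described covers follow-up only, so extend the request to registrations before the self-test.
4. Add the same exclusion to remaining Cohort 1 invitations if feasible. If the parent trial's eligibility already has this effect, state so.
5. Leave Cohort 3 unchanged. It is a referred diagnostic cohort with a different purpose.

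The cost is a few participants lost from the yield analysis and a slightly wider registry request. Self-testing and clinic procedures stay as they are.

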### Screening tests and self-testing

Participants in all three cohorts will be provided with home urine self-testing kits produced and supplied by Testcard. The kit contains 6× Roche Combur 5 HC test strips for the graduated determination of glucose, leucocytes, nitrites, protein and erythrocytes. Blood and glucose will be tested for primary study purposes. The other three parameters (leukocytes, nitrite, protein) will be analysed as part of an exploratory objective.

Participants will record six continuous days of test strip results via a bespoke study App or study freephone service. Prior to commencing self-testing, participants will complete a bladder symptom questionnaire (a modified and unvalidated version of the Urinary Tract Infection Symptom Assessment (UTISA) Questionnaire).^25^ The questionnaire will collect demographic data and information on bladder symptoms within the past 4 weeks including presence of VH. The questionnaire will be pseudonymised and all data pertaining to the questionnaire will be kept separate from urine self-testing results until the end of the trial. The app will capture a digital photograph of the test strip, which will be interpreted by a research nurse against the Roche Combur 5 HC colour chart. Test strip results will not be available to participants at the point of self-testing.

It is anticipated and expected that some participants in the study population will either not have a smartphone, or will not be confident in using a mobile App. A study freephone service will therefore be available as an alternative option for recording self-test results. The freephone service will be an automated system whereby participants use their keypad to enter their responses to the questionnaire and test strip results. The freephone service requires confirmation of the test strip colour result by the participant against the Roche Combur 5 HC colour chart, whereas App users will simply take a photograph of their completed test strip which will be submitted for interpretation by a research nurse.

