9.2.1. Haematuria positive/symptoms positive

9.2.2. Haematuria negative/symptoms positive

9.2.3. Haematuria positive/symptoms negative

9.2.4. Haematuria negative/symptoms negative

10. Recruitment rates will be measured via the number of invitations sent out versus uptake.

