### Statistical analysis

We will present estimates of percentages, with 95% Wilson CIs, on a per cohort basis for the three trial endpoints that will allow assessment of feasibility and inform the subsequent more definitive trial. We will estimate acceptability (proportion of invitees consenting and returning a test strip), compliance (proportion of participants returning at least three or all six test strips), haematuria and glucosuria, proportion of positive outcomes for those referred to the Early Detection Clinic (positive cytology and/or USS for haematuria and HbA1c for glycosuria). We will assess the levels of BCa in the cohort identified by Early Detection clinic and at 3 years using National Disease Registration Service (NDRS, formerly NCRAS) and the accuracy of the haematuria test results including PPVs and NPVs for Cohorts 1 and 2 only. The urinary symptoms questionnaires will be summarised by cohort, by the proportions with each urinary symptom, and by overall urinary symptoms using mean, SD, median, minimum, maximum and quartiles. Missing values will be imputed as no symptom.

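### Imputing missing symptom answers as no symptom biases every symptom proportion in primary outcome 7 downwards; missing answers should be shown separately

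*Protocol article*

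**What the plan says.** Under Screening tests and self-testing, the protocol article has participants in all three cohorts complete a modified, unvalidated symptom questionnaire before they start on the strips. Besides demographic data, it collects "information on bladder symptoms within the past 4 weeks including presence of VH", where VH is visible haematuria. Answers are entered in the App or on the freephone keypad.

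Under Primary outcomes, outcome 7 is the symptom scores from this questionnaire. Outcome 9.2 is the predictive value of symptoms combined with the strip result, in four cells that end with "Haematuria negative/symptoms negative".

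Under Statistical analysis, the questionnaires are to be "summarised by cohort, by the proportions with each urinary symptom", and by overall symptoms using the usual summary statistics. The next sentence sets the rule for blanks: "Missing values will be imputed as no symptom". The same section names 95% Wilson intervals for estimated percentages.

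**The concern.** A blank is not a no. Coding it as one assumes that nobody who skipped an item had the symptom, and then counts that person in the denominator as if the answer were known. The error has one direction for every item, VH included, and it lowers any overall score built from the items. A confidence interval computed on the filled-in data does not show it, because the interval treats the imputed answers as observed.

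What is at stake is the description of symptoms in the invited populations, which is a primary outcome of a feasibility study meant to inform a larger trial. If the same coding is carried into outcome 9.2, people whose symptom status is unknown enter its symptom-negative cells. The article commits to this rule, so it is not a detail left open for a later analysis plan.

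**Working it through.** The article gives no symptom prevalence and no missing rate, so there is no figure of its own to reproduce. Both are assumed below. The sample sizes are the estimated enrolments under Sample size(s): 800, 1200 and 500 for Cohorts 1, 2 and 3.

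**1. Direction.** Filling blanks with no symptom counts only the symptomatic people who answered and divides by everyone. That count cannot exceed the number truly symptomatic, so the result can equal the full-data proportion or fall below it, whatever the reason for the blanks.

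**2. Size.** Let p be the true prevalence and m the share missing, with non-answerers like answerers. Then reported = (1 − m)p and bias = −mp. At p = 20%:
- m = 5%: 0.95 × 20 = 19.0%
- m = 10%: 0.90 × 20 = 18.0%
- m = 20%: 0.80 × 20 = 16.0%

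**3. Against sampling error.** The Wilson half-width is h = z/(1 + z²/n) × √[p(1 − p)/n + z²/(4n²)], with z = 1.96. For p = 0.20 and n = 800: (1.96/1.0048) × √(0.000200 + 0.0000015) = 0.0277, or 2.77 points. The bias reaches h when m = h/p.

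| p | n | h (points) | m at which bias = h |
|---|---|---|---|
| 20% | 500 | 3.50 | 17.5% |
| 20% | 800 | 2.77 | 13.8% |
| 20% | 1200 | 2.26 | 11.3% |
| 50% | 500 | 4.37 | 8.7% |
| 50% | 800 | 3.46 | 6.9% |
| 50% | 1200 | 2.82 | 5.6% |

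The rule therefore does most harm to common symptoms in the larger cohorts.

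**4. VH, a rare item.** At an assumed 2% VH, m of 5% to 20% gives a bias of 0.02 × 0.05 = 0.1 to 0.02 × 0.20 = 0.4 points, which is small in absolute terms. The share of a no-VH group that truly had VH is vm/(vm + 1 − v), where v is the VH prevalence. At v = 2% and m = 10% this is 0.002/0.982 = 0.204%. Take bladder cancer risk as 0.72% without VH (17/2356, the British screening study cited in the introduction) and an assumed 10% with VH. The group's rate becomes 0.00204 × 10% + 0.99796 × 0.72% = 0.739%, so this effect is also small.

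**5. Cost of using answerers only.** The interval widens by about 1/√(1 − m): 2.6% at m = 5%, 5.4% at 10% and 11.8% at 20%.

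**The case against.** The best defence is that blanks may be rare. The Consent and Screening tests sections place the questionnaire before self-testing, in the App or on the keypad, and if the system requires each answer the rule will hardly operate. The 5–20% range is assumed. Extending the rule to outcome 9.2 is an inference, since the sentence directly follows the questionnaire summary. If people skip items because they have nothing to report, the rule would be close to right. All of this limits the size of the problem. It does not make the rule a good default, because the article gives no ground for reading a blank as a no.

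A reader might also infer two stronger points that the article does not support.

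- **That outcomes 3, 5 and 8 are wrong because they are not split by declared VH.** Research need does speak of "detection of haematuria in asymptomatic individuals at high risk of mortality from the cancer", and Cohorts 1 and 2 have no VH exclusion. But Aims 1 and 2 are framed for a screening-engaged and a high-risk community population, and outcome 8 ("proportions of BCa cases and corresponding stage in identified participants") for the tested population. Questionnaire and strip data are kept apart only until the trial ends, so an analysis plan, not shown here, can still add the split. A VH-free group is not an asymptomatic one either, since the introduction says that many patients have irritative symptoms before VH. For outcome 3, with v = 1–5%, strips positive in 50–100% of those with VH and in 20% of others (all assumed), the shift is v(q − 0.20), where q is strip positivity with VH. It runs from 0.01 × 0.30 = 0.3 to 0.05 × 0.80 = 4.0 points and passes 2.77 only near the top. For outcome 8, 2% VH at 10% risk gives 0.02 × 0.10 + 0.98 × 0.72% = 0.91%, inside the 0.39–1.32% Wilson interval around 0.72% at n = 1400 (800 plus half of 1200). The share of cancers from people with VH would be 0.20/0.91 = 22%, which makes a descriptive table worthwhile but shows no error.
- **That a declared VH gets no clinical response.** The article describes none. However, the information sheet, the App and freephone wording and the full protocol are not shown, so the gap cannot be established.

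**Conclusion.** The imputation rule is a real but minor fault. Its direction is certain: no symptom proportion in outcome 7 can be raised by it, and any can be lowered. Its size is m × p if non-answerers resemble answerers. For symptoms at 20–50% prevalence and n = 800, it exceeds sampling error above about 14% and 7% missing respectively. For a rare item such as VH it stays small. The missing rate and the prevalences are assumptions, and the Wilson half-width serves as a yardstick, since the article does not say outright that each symptom item will carry an interval. The effect on outcome 9.2 is conditional on the same coding being used there. The absence of a VH split and the handling of a declared VH are not part of this finding.

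**What to change.** Replace the one sentence under Statistical analysis. State instead that the number missing will be reported for each item and cohort, that symptom proportions with 95% Wilson intervals will be computed among those who answered, and that missing will appear as its own category in outcomes 7 and 9.2. Keep missing coded as no symptom at most as a labelled sensitivity analysis. The overall symptom summary needs a matching rule for partly completed questionnaires, which can sit in the analysis plan.

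The change uses data already collected and applies to everyone enrolled. Its price is the smaller denominator and the widening shown above. Proportions among answerers are themselves unbiased only if the blanks are uninformative, so the missing counts must stay visible beside them.

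Optionally, and not as a correction, add a descriptive table of outcomes 3, 5 and 8 by declared VH in Cohorts 1 and 2, noting that differences will probably lie within sampling error.
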